### Data management

The study is conducted through the online platform 7 Cups, which has all the necessary infrastructure to provide the growth path, listener training, and participant communication. After questionnaire and assessment data are collected via LimeSurvey, it is transferred to a secure database on the IPU servers, accessible only to authorised personnel. Routine backups are conducted to ensure data safety and confidentiality. Data handling by 7 Cups, IPU, and LimeSurvey complies with the GDPR and is supervised by the 7 Cups HOR and the data protection officer of IPU. Throughout the study, general data management, including exclusions, recruitment, dropout, communication, and participant rate is meticulously recorded. Data collection commenced on 30-08-2023 and last patient/last visit is projected to conclude on 31-03-2024. Double data entry will not be conducted as all data for this study is collected digitally and digital data entries are restricted to valid entries only.

### Statistical methods

For statistical analyses and handling of missing data, descriptive statistics and estimation of intervention effects are planned following recognised guidelines. Appropriate regression methods shall be used, depending on the outcome parameters’ distributional characteristics. To estimate intervention effects, we intend to conduct generalised linear mixed models of primary, and secondary parameters, adjusted for potential covariates (e.g., gender, age categories, socioeconomic status) as fixed effects. The exact choice of regression method shall consider the distributional characteristics of the outcome parameters of interest. Concerning the management of missing data, we aim to minimise bias through thorough planning and active data review. A differentiation shall be made between missing data due to partial participation and loss to follow-up, and appropriate statistical methods shall be considered to address missingness.

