### Outcomes

Our outcomes are divided into primary and secondary outcomes. We provide a full list of assessment instruments in Table 1 which also includes the list of primary and secondary endpoints. The primary outcome of our study is the Kessler Psychological Distress Scale 6 (K6), which is a standardised self-reported outcome assessment tool used to measure global non-specific psychological distress with questions relating to depressive and anxiety symptoms. We selected the K6 for its brevity and validation in community-based samples ranging from subclinical to clinical distress [41, 42]. Although floor effects are a possibility in individuals without any significant distress, our preliminary assessments and data from 7 Cups suggest that a noteworthy proportion of participants have mild to moderate distress, making the K6 a pragmatic primary outcome measure. The primary endpoint of the study is the scores of the K6 assessment instrument, which consists of 6 items asking participants to rate their emotional states on a 5-point Likert scale ranging from ‘All the time’ to ‘None of the time’. The K6 is a widely used and accepted assessment instrument for measuring mental health-related intervention outcomes with confirmed reliability and validity. The K6 has good psychometric properties in the general population and is considered reliable with excellent internal consistency reliability of 0.89 [41, 42].

**Table 1 Tab1:** Measures and timepoints

Measure	Time point			References
	Pre	Post	Follow-Up (Post + 2 weeks)	
K6	x	x	x	Cornelius et al., 2013
PSS-4	x	x	x	Warttig et al., 2013
PHQ-4	x	x	x	Kroenke et al., 2003
UMUX-LITE		x*		Finstrad, 2010
MDMQ (4-item)	x	x	x	Steyer et al., 1997
Qualitative questions		x		
Sociodemo- graphic and other general information	x			

Abbreviations: K6, Kessler Psychological Distress Scale 6; PSS-4, Perceived Stress Scale-4; PHQ, Patient Health Questionnaire; UMUX-LITE, Usability Metric for User Experience; MDMQ, Multidimensional Mood State Questionnaire

*is not completed by subjects in waitlist condition

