The secondary outcomes of the study are the Perceived Stress Scale 4 (PSS-4) [43], the 4-item Patient Health Questionnaire (PHQ-4) [44], the 2-item Generalised Anxiety Disorder Questionnaire (GAD-2) [44], and the Multidimensional Mood State Questionnaire (MDMQ, good-bad subscale) (English-language version of MDBF) [45]. Outcome data are collected through self-reported questionnaires and will be analysed to assess the effectiveness and feasibility of the intervention. In addition, a qualitative questionnaire is used to gather further information, feedback, and details about the experience and perceived quality of the intervention [46–48] (see Appendix A for a full list of qualitative and sociodemographic questions). Sociodemographic data are gathered during the baseline assessment for all participants and include age, gender, country of living, and level of education. Participants also complete questions to provide further details of any other interventions used during the intervention.

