
### Data collection, management and analysis

The study employs a pre-post-follow-up design for the assessments. These assessments are facilitated through LimeSurvey, a General Data Protection Regulations (GDPR) compliant tool. The links for the t0 pre-assessment are sent to participants after being assigned to their respective conditions by the 7 Cups HOR. Our research team and the 7 Cups HOR monitor the progress of the participants and send them a link to complete the t1 post-assessment survey upon completion of the growth path, listener training, or 4 weeks into the waitlist condition. Participants who stop progressing on the growth path, listener training, or assessments for more than a week are sent reminders by the 7 Cups HOR. A link for the t2 follow-up assessment is sent two weeks after the completion of the t1 assessment. After completing the t2 assessment, the member and listener waitlist participants are sent the link to the growth path or listener training, respectively. If participants want to opt out of the study or request their assessment data to be deleted, they are instructed to contact the 7 Cups HOR or the Data Protection Officer at the IPU. After data cleaning, all participant UICs will be deleted, resulting in a fully anonymized dataset for further analysis.

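### The plan does not say how baseline K6 enters the effect model, and two of the three natural model forms would lose precision

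*Protocol article*

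**What the plan says.** Under Statistical methods, the protocol article states "we intend to conduct generalised linear mixed models of primary, and secondary parameters", and these are to be "adjusted for potential covariates (e.g., gender, age categories, socioeconomic status) as fixed effects". The Abstract repeats the same list. The section leaves the form of the model open: "The exact choice of regression method shall consider the distributional characteristics of the outcome parameters of interest". It does not say whether t0 is a covariate, one of the repeated responses, or unused.

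On the data, the Outcomes section states "The primary endpoint of the study is the scores of the K6 assessment instrument", and the data collection section states "The study employs a pre-post-follow-up design for the assessments". Table 1 schedules K6, PSS-4, PHQ-4 and the four-item MDMQ at pre, post and follow-up, so each of these scales has its own t0 value.

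On timing, the data collection section states "The links for the t0 pre-assessment are sent to participants after being assigned to their respective conditions by the 7 Cups HOR". The Allocation section accepts that participants know their condition.

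**The concern.** Adjustment is the one feature of the effect model that the article illustrates, and every illustration is demographic. The baseline value of the outcome is usually the strongest candidate for adjustment, and here it is already collected. The article itself treats it as relevant: the Discussion warns that people who start with little distress may have no room to improve on K6. Eligibility sets no distress threshold, and the Allocation section describes no stratification by distress, so baseline K6 can vary widely and can differ between arms by chance.

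What is at stake is the width of the interval for the K6 difference in a trial that expects about 37 or 38 completers per arm, and how far a chance gap at t0 carries into the estimate. If the choice between model forms is left until the data are seen, it also becomes a data-driven choice between estimates of different precision.

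**Working it through.** **Inputs from the article.** 50 per group, four groups, 25% attrition (Sample size). The stated total reproduces: 4 × 50 = 200. Expected completers per arm: 50 × 0.75 = 37.5. The article gives no alpha, power, effect size or SD, so there is no power figure to reproduce.

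**Assumed inputs.** The correlation r between K6 at t0 and at t1 is not given. I take 0.5 to 0.7 as the main range and show 0.3 and 0.8 as extremes. I also assume a continuous outcome with equal SD at t0 and t1, 95% two-sided intervals, and complete data on the 37.5 per arm. Results are in SD units.

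**Formulas** (half-width of the 95% interval, n = 37.5):
- t1 only: 1.96 × √(2/n) = 1.96 × 0.2309 = 0.453
- difference in change (group-by-time contrast, free baseline means): 0.453 × √(2(1 − r))
- t0 as covariate: 0.453 × √(1 − r²)

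Equivalent extra participants, relative to t0 as covariate:
- difference in change: 2(1 − r)/(1 − r²) − 1 = 2/(1 + r) − 1
- t1 only: 1/(1 − r²) − 1

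| r (assumed) | t1 only | change | t0 covariate | extra, change | extra, t1 only |
|---|---|---|---|---|---|
| 0.3 | 0.453 | 0.536 | 0.432 | 54% | 10% |
| 0.5 | 0.453 | 0.453 | 0.392 | 33% | 33% |
| 0.6 | 0.453 | 0.405 | 0.362 | 25% | 56% |
| 0.7 | 0.453 | 0.351 | 0.323 | 18% | 96% |
| 0.8 | 0.453 | 0.286 | 0.272 | 11% | 178% |

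**Check by simulation** (4,000 runs, 37 per arm, known covariance for the common-mean model; standard error of the t1 effect):

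| r | t1 only | change | t0 covariate | common baseline mean |
|---|---|---|---|---|
| 0.5 | 0.233 | 0.233 | 0.204 | 0.203 |
| 0.7 | 0.233 | 0.181 | 0.168 | 0.167 |

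A mixed model is therefore not enough by itself. With free baseline means it gives the change contrast, which at r = 0.5 is no better than ignoring t0. With a common baseline mean it matches covariate adjustment.

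**Chance imbalance.** The SD of the baseline difference between arms is √(2/37.5) = 0.23 SD, so a gap above 0.2 SD in either direction occurs with probability 2 × [1 − Φ(0.2/0.231)], about 39%. A t1-only estimate absorbs r times the gap: at r = 0.5, 0.5 × 0.2 = 0.10 SD.

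**Effect of t0 after allocation.** Suppose knowing the condition shifts reported t0 K6 in one arm by δ and leaves t1 alone. The t0-covariate estimate moves by −rδ, the change estimate by −δ, and the t1-only estimate not at all. Since r is below 1, adjustment is less exposed than the change contrast, but it is not immune.

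**The case against.** The strongest reply is that the article decides nothing here. The covariates are called potential and introduced as examples, the regression method is left open, and a mixed model of pre-post-follow-up data may well carry t0 as a response with a common mean, in which case nothing is lost. The exact covariate set often sits in a statistical analysis plan, and none is shown. No passage proposes a t1-only analysis, so the larger figures in that column describe a model nobody has announced. The trial is declared exploratory, with no power claim that depends on adjustment.

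Most of this stands. A reader might infer that the plan excludes baseline K6; the text does not support that, because an example list excludes nothing. A reader might also infer that baseline K6 is shown to be the most prognostic variable; the article gives no correlation. What remains is that the article does illustrate its adjustment, does so only with demographics, and leaves unstated a choice that changes precision materially.

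A reader might further infer that socioeconomic status is a missing variable that weakens the analysis. The listed sociodemographic items "include age, gender, country of living, and level of education". Education is a common indicator of socioeconomic status, and the reader is sent elsewhere for the rest ("see Appendix A for a full list of qualitative and sociodemographic questions"); that appendix is not shown. Absence cannot be established, and an undefined socioeconomic item would not cause the loss computed here. No loss from using age in categories can be computed from the article either.

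The timing of t0 is a fair objection to any use of it. It limits the gain in cleanliness, but it counts more heavily against a change contrast than against covariate adjustment.

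**Conclusion.** The point holds as a specification gap with a conditional cost. The article does not say how t0 K6, or the t0 value of each secondary scale, enters the effect model. If the model reads off a difference in change, the loss relative to baseline adjustment equals 33%, 25% or 18% more participants at r = 0.5, 0.6 or 0.7. If t0 is ignored, it equals 33%, 56% or 96%. If a common baseline mean is already intended, there is no loss. The correlations are assumed, and the figures apply to a continuous outcome with equal variances and 37.5 completers per arm. The precision gain also presupposes that t0 is not distorted by knowledge of the condition, which the order of procedures does not guarantee. Nothing here invalidates the trial, but it is worth settling before the data are analysed.

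**What to change.** State in the analysis text that, for members and listeners separately, K6 at t1 and t2 is modelled on group, time, group-by-time, and K6 at t0 with its time interaction. Say that each secondary scale is treated the same way with its own t0 value. Demographic covariates may stay as additional terms.

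Use the version with t0 in the response and a common baseline mean only if t0 precedes allocation, because only that order guarantees equal expected means at t0. As the article describes t0 as sent after assignment, report with the result that the baseline may have been influenced by allocation. A t1-only estimate alongside would show how much the answer depends on t0. Also state how participants with no t0 value are handled, since they drop out of a model that uses t0 as a covariate.

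As a minor clarification, name the collected item that stands for socioeconomic status.

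The cost is a few sentences of analysis text and no new data. The change does not repair the timing of t0; that would need a change in conduct, which the stated recruitment dates may no longer allow.

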### Monitoring

The Principal Investigator (PI) assumes responsibility for several key aspects of the study. The PI is in charge of any interim analyses and stopping guidelines, maintaining exclusive access to these interim results and making the final decision to terminate the trial. The PI also establishes plans for collecting, assessing, reporting, and managing solicited and spontaneously reported adverse events and other unintended effects of the intervention or participation. This approach upholds the integrity and transparency of the study while acknowledging the responsibilities of the PI.

This study does not include a formal, dedicated measure of adverse events. However, in line with 7 Cups safety protocols, any participant presenting signs of self-harm risk or crisis is escalated to crisis resources and local emergency services if needed. The PI monitors all communications from the 7 Cups Head of Research (HOR) related to adverse events. If serious adverse events occur, they are documented and reviewed as part of the ethical oversight.

### Ethics

In terms of ethics and dissemination, the study is designed with a strong emphasis on ethical considerations and transparency. Although no formal Data Monitoring Committee was established due to the low-risk nature of the intervention, provisions are in place for the premature termination of the study under specific circumstances, such as insufficient participant recruitment, significant changes in 7 Cups practices, or early evidence of harm or benefit from the growth path or listener training. Training was completed by all authorised personnel who are involved in the study to ensure responsibilities, and protocols are clear and understood. Despite the minimal anticipated risk, the study thoroughly assesses any potential harm. Serious Adverse Events (SAEs) that occur during the study, including those related to suicide attempts or completed suicide, are continuously monitored and responded to by 7 Cups. Internal audits are carried out to verify all procedures, including recruitment, consent, enrolment, and data collection.

Data confidentiality and secure coding are prioritised. Participants’ data are only accessible to authorised personnel and securely stored. The complete dataset, once finalised, will be transferred to the principal investigator, with limited access granted to other IPU members for analysis.

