
Similar to digitally delivered interventions of family therapy interventions [16, 17], digitally delivered ST in the form of online self-help interventions (OSIs) may be one such promising path. This approach is particularly promising as digital delivery continues to advance and may help to overcome some of the common impediments to the worldwide delivery of psychotherapy such as limited access [18, 19], cost, and stigma [20]. While ST has been validated primarily in clinical populations, data suggest its approach may also benefit non-clinical users who experience stress or mild psychological distress [2, 5, 21–23]. Because 7 Cups members and listeners do not necessarily have formal diagnoses, this study seeks to determine if an ST-informed approach can be feasibly applied and beneficial to a broader population, including subclinical or undiagnosed distress. OSIs can be broadly divided into guided and unguided modes of self-help, with the former showing better efficacy than the latter [24]. This distinction notwithstanding, unguided OSIs are effective in the treatment of anxiety [25], depression [26], the prevention of suicides [27], and numerous other mental health disorders and conditions [28]. From a public health perspective, OSIs are particularly interesting as they promise to address several obstacles to conventional mental health care provision and harness patients’ capacities for self-help [29]. Additionally, their scalability might facilitate the provision of services to target groups that could otherwise not be reached [30]. While there still appears to be some level of discrepancy in terms of perceived acceptability in patients and practitioners (the latter rating acceptability lower than the former) [28], OSIs are particularly effective within so-called “blended care” approaches, integrating OSIs with face-to-face treatment [31]. Another way in which OSIs might prove a useful addition to existing modes of treatment is within a so-called “stepped care” approach where OSIs function as a first “step up” following prevention and diagnostics and preceding other forms of treatment such as face-to-face psychotherapy [32]. Platforms like “7 Cups” (https://www.7cups.com) offer self-help, text-based paraprofessional support, and signposting to professional services, which aligns with some recommendations and prior research in digital mental health research on the 7 Cups platform [1]. Further, systematic reviews indicate that platforms combining self-guided digital content with human support can be especially promising (see Sin et al. [33] for a general review of digital interventions). Although systemic therapy is commonly delivered to couples, families, or other relational systems, it is also the case that individual-focused ST adaptations can be used to leverage systemic principles in an individual context (e.g., encouraging an individual to explore relational patterns and multi-perspective taking). Our digital modules similarly focus on these relational perspectives and interactions, even though each participant completes the program individually. Our study focuses on the feasibility and exploratory efficacy of such an approach, rather than making conclusive claims about its effectiveness.

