## Methods and design

### Overview of research project and study design

The main components of our study are:

i)An exploratory, randomised, controlled trial following the definition of the National Institute for Health Research UK (NIHR UK) in a natural setting, pre-post-follow-up design with two parallel comparisons:
the 2 arm ST-informed OSI (growth path) intervention compared with a waitlist comparator condition among 7 Cups members, and,the 2-arm ST-informed paraprofessional provider/listener training compared with a waitlist comparator condition among 7 Cups listeners.

Each comparison uses a 1:1 allocation ratio. Figure 1 displays participant flow in each sub-study, including randomization to intervention vs. waitlist and subsequent follow-up assessments. Although this is not a fully powered randomized controlled trial (RCT), randomization will be used to test the procedure and to gather exploratory efficacy data.

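### Early termination for benefit, decided by the only person who sees interim results, does not fit an exploratory feasibility trial, and the statements on harm need to be reconciled

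*Protocol article*

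**What the plan says.** **Termination.** The Ethics section allows premature termination for insufficient recruitment, for significant changes in platform practice, or on "early evidence of harm or benefit from the growth path or listener training". It also states that "no formal Data Monitoring Committee was established due to the low-risk nature of the intervention".

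**Who decides.** Under Monitoring, "The PI is in charge of any interim analyses and stopping guidelines", with that person "maintaining exclusive access to these interim results and making the final decision to terminate the trial". The article gives no number, timing, outcome or threshold for an interim look.

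**Purpose.** The Background says the study addresses feasibility and exploratory efficacy "rather than making conclusive claims about its effectiveness". The design overview says "Although this is not a fully powered randomized controlled trial (RCT), randomization will be used to test the procedure and to gather exploratory efficacy data". The Discussion names feasibility and preliminary efficacy data as the primary aim and leaves confirmation or refutation of efficacy to larger trials.

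**Harm.** Monitoring gives the principal investigator plans for both solicited and spontaneously reported adverse events, then says: "This study does not include a formal, dedicated measure of adverse events". Serious events are to be documented and reviewed. The Ethics section says that "the study thoroughly assesses any potential harm" and that the platform monitors serious events continuously. Table 1 lists no adverse-event instrument. K6, PSS-4, PHQ-4 and MDMQ are collected at all three time points, and only UMUX-LITE is marked as omitted for the waitlist.

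**The concern.** A trial that does not claim to settle efficacy at full size cannot settle it on part of the data. A benefit stop would therefore act on evidence that the plan itself calls inconclusive, and it would cut short the recruitment, adherence and follow-up data that the trial mainly exists to collect. Estimates taken at such a stop are on average too large, and they could be used to plan the larger trial that the Discussion calls for. The article describes no independent person who sees the same results.

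The harm wording carries a different risk. A reader of the final report could take an absence of reported harm as the outcome of systematic assessment, when most of what is described is escalation and spontaneous reporting through the platform.

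**Working it through.** **1. The plan's own figure.** Two comparisons × two arms × 50 = 200, which matches the Sample size section. With the stated 25% attrition, 50 × 0.75 = 37.5 per arm are expected to complete. No alpha, sidedness, SD or target effect is given, so everything below is illustrative. Assumptions: two-sided 5%, differences in SD units, normal approximation, no baseline adjustment, and one unadjusted look at half the data. That means 25 per arm without attrition or 18.75 per arm with it.

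**2. Observed difference needed at the look.** Threshold = 1.96 × √(2/n).
- n = 25: 1.96 × 0.283 = 0.55 SD
- n = 18.75: 1.96 × 0.327 = 0.64 SD

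**3. What would be reported after such a stop.** With true effect d and standard error s = √(2/n), let a = 1.96 − d/s. The chance of stopping for benefit is 1 − Φ(a), and the mean estimate given a stop is d + s·φ(a)/(1 − Φ(a)). Results by simulation:

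| True effect (SD) | n per arm at look | Chance of benefit stop | Mean estimate if stopped (SD) |
|---|---|---|---|
| 0 | 25 | 2.5% | 0.66 |
| 0 | 18.75 | 2.5% | 0.76 |
| 0.2 | 25 | 10.5% | 0.69 |
| 0.2 | 18.75 | 8.9% | 0.79 |
| 0.5 | 25 | 42% | 0.76 |
| 0.5 | 18.75 | 33% | 0.86 |

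For a true 0.2 SD the exaggeration is 0.69/0.2 ≈ 3.5-fold to 0.79/0.2 ≈ 4-fold. For a true 0.5 SD it is about 1.5- to 1.7-fold.

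**4. Type I error.** Simulated equally spaced looks at |Z| > 1.96, counting the final one, give 8.3% for two looks, 10.7% for three and 14.2% for five, per comparison and two-sided. On the benefit side alone, two looks give 4.2% against 2.5%. Over both comparisons, two looks give 1 − (1 − 0.083)² = 15.9%. Two single-look comparisons already give 1 − 0.95² = 9.75%, so only the excess of about 6 percentage points comes from looking early.

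**5. Harm.** Side by side, the article says that events are solicited, that there is no formal, dedicated measure, and that harm is assessed thoroughly. The first two can coexist if events are solicited informally, but the article does not say how. Neither supports the third as written. What small numbers can show is limited even with full capture:
- An event with 2% risk appears at least once among 50 with probability 1 − 0.98⁵⁰ = 64%.
- Zero events in 50 leaves a one-sided 95% upper bound of 1 − 0.05^(1/50) = 5.8%.

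**6. K6 worsening as a description.** Counting any higher score mostly counts noise. With the reported reliability of 0.89 and an assumed SD of 4 to 5 points, the SD of a pure-error change is SD × √(2 × 0.11) = 0.47 SD, or 1.9 to 2.3 points. About 40% would then score at least one point worse with no true change. The 95% interval for a difference between arms at 40% is ±1.96 × √(2 × 0.4 × 0.6/50) = ±19 percentage points, or ±22 with 37.5 per arm. A change beyond error would be about 1.96 × 0.47 SD, or 3.7 to 4.6 points. The 0.89 is internal consistency, so this is only a rough guide.

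**The case against.** **No interim analysis is scheduled.** Monitoring speaks only of any interim analyses, and a boundary could sit in an analysis plan that is not shown. This stands: the missing boundary is not part of the point, and the figures are conditional. A boundary would not remove the mismatch between a benefit stop and the disclaimed efficacy claims. The Dissemination section also says that the article gives public access to the full protocol.

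**The thresholds are not properties of this plan.** Mixed models are planned and K6 is measured at baseline. If the model conditions on baseline with an assumed correlation of 0.5 to 0.7, the thresholds shrink by √(1 − r²), to roughly 0.40 to 0.55 SD. This stands.

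**Stopping does not always exaggerate.** A reader might infer that any benefit stop must overstate the effect. It need not. At 25 per arm with a true effect of 0.8 SD, Φ((0.8 − 0.554)/0.283) = 0.81 of looks would stop, and (0.81 − 0.50)/0.81 ≈ 38% of those estimates lie below the truth. The bias is an average tendency, and it is severe when the true effect is small.

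**Harm can be seen.** A reader might infer that the trial cannot show harm, or has no data comparing arms. The article does not support that. Serious events are documented and reviewed, and symptom scores are collected in both arms at three time points. It also does not say there is no adverse-event measure at all, only no formal, dedicated one.

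**The clause may be spent.** Data management projects the last visit for 31-03-2024. If that held, disclosure replaces prevention.

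**Conclusion.** The point holds in limited form. Benefit as a termination ground, left to one person with sole access to interim results and no monitoring committee, conflicts with the article's own description of an exploratory, not fully powered, mainly feasibility study. This is a stated rule, not an omitted detail. Its size depends on looks that may never have been made. Under one unadjusted half-way look at two-sided 5% without baseline adjustment, significance needs about 0.55 to 0.64 SD, a true 0.2 SD is reported on average as about 0.7 to 0.8 SD, and type I error is about 8.3% per comparison. The 15.9% over both comparisons should not be charged to the clause, since most of it comes from having two comparisons, in separate populations. Because the trial disclaims confirmatory conclusions, the exaggerated estimate and the lost feasibility data matter more than the error rate.

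The harm statements are inconsistent in wording. Harm is captured through crisis and serious-event channels and through symptom scores, which is weaker than thorough assessment but is not nothing.

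**What to change.** 1. In Ethics, delete benefit as a ground for early termination and leave the other grounds as they are. State that no between-arm comparison of K6 is made before all t2 data are in. If one was made, disclose when, by whom and with what consequence. The cost is one sentence and the option of an early benefit stop, which an exploratory trial hardly needs.
2. Reconcile the statements on solicited events, on the absence of a formal measure and on thorough assessment. Say how events were solicited, if they were. Otherwise describe capture as spontaneous reports plus platform escalation. The cost is wording only.
3. Describe K6 worsening by arm at t1 and t2 from data already collected, with the between-arm difference and its confidence interval. Preferably use a change larger than measurement error, fixed before the arms are compared. State the low precision, so that the table is not read as evidence of no harm. The cost is one table.
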